### Statistical analysis

2.12

The measured variables, including the primary and secondary outcomes, will be assessed using the full analysis set based on intention-to-treat principles. The per-protocol analysis set will be used for the sensitivity analysis. Values for baseline characteristics in both groups will be expressed as means and standard deviations for continuous variables satisfying the normal assumption or medians and interquartile ranges for non-normal data. Frequencies and percentages will be used to represent categorical variables. Baseline differences between groups will be assessed using an independent 2-sample *t* test or the Wilcoxon rank-sum test for continuous variables and the Chi-square test or Fisher exact test for categorical variables.

A mixed-effect model repeated measure (MMRM), which sets participants as a random factor and the group and visit as fixed factors, will be performed to analyze between-group differences in the primary and secondary outcome measures. A subgroup analysis will also be performed to explore differences in the effects of GGTCS according to the cold-heat pattern, Sasang constitutional type, and symptom severity. Student paired *t* tests or Wilcoxon signed-rank tests will be performed to analyze differences before and after treatment in each group, and repeated measures analysis of variance will be used to assess differences between groups at each visit. The level of significance will be set at 0.05 (2-tailed), and all analyses will be performed by an independent statistician using SAS version 9.4 (SAS institute. Inc., Cary, NC).

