**Methods and analysis::**

To investigate the clinical efficacy and safety of GGTCS for the treatment of CRS, a randomized, double-blind, placebo-controlled, parallel group, clinical trial has been designed. A total of 58 participants with CRS will be recruited and randomly allocated to a GGTCS or placebo group in a 1:1 ratio. The participants will be administered GGTCS or placebo granules 3 times a day for 8 weeks. Data will be collected from the participants at baseline and at 1, 2, 4, and 8 weeks after random allocation. The primary outcome measure will be the mean change in the Sino-Nasal Outcome Test-22 score from baseline to 8 weeks. The secondary outcomes will include the Total Nasal Symptom Score, EuroQoL 5 Dimensions 5 Levels score, Nasal Endoscopy Index, Lund-Mackay score, and total serum immunoglobulin E level.

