#### Primary outcome

2.6.1

The primary outcome will be the mean change in the SNOT-22 score from baseline to 8 weeks.^[17]^ The SNOT-22 is a validated, rhinosinusitis-specific, quality-of-life instrument comprising 22 items encompassing 4 subscales: nasal symptoms, ear and facial symptoms, sleep condition, and psychological domains.^[18]^ The participants will be asked to score a list of 22 symptoms and mark the 5 most important items.

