### Sample size

2.9

No clinical trial has been conducted to evaluate the effects of GGTCS on the SNOT-22 score for patients with CRS. A formal power calculation has not been performed because this study will evaluate the feasibility to calculate a required sample size for subsequent definitive randomized clinical trials. On the basis of recommendations by a previous study,^[23]^ a minimal effect size of 0.25 and dropout rate of 20% have been assumed for this trial. Thus, a total of 58 participants, 29 in each group, will be recruited.

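### Fitted with the terms listed, the primary MMRM gives a group effect averaged over visits and not the week-8 change in SNOT-22 that the protocol defines as primary.

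*Protocol article*

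**What the plan says.** Section 2.6.1 ties the primary outcome to one time point: "The primary outcome will be the mean change in the SNOT-22 score from baseline to 8 weeks". The abstract gives the visit schedule: "Data will be collected from the participants at baseline and at 1, 2, 4, and 8 weeks after random allocation". Which of these visits record SNOT-22 is set out in Table 1, which is not available here.

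Section 2.12 names a mixed-effect model for repeated measures as the between-group analysis of both primary and secondary outcomes. It describes that model as one "which sets participants as a random factor and the group and visit as fixed factors, will be performed to analyze between-group differences". No interaction and no time-specific contrast is mentioned, and the text does not say whether the response is the raw score or the change from baseline.

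Later in the same paragraph a second between-group method appears: "repeated measures analysis of variance will be used to assess differences between groups at each visit". It is not linked to the primary outcome, and no order of priority between the two methods is stated.

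**The concern.** The outcome definition asks how far the groups differ in their change at week 8. The listed terms answer another question. With group and visit as main effects only, the model carries one treatment difference that applies equally at every visit. Asking the software for the difference at week 8 returns that same number.

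If the effect of the herbal formula builds up over the 8 weeks, the headline estimate, confidence interval and p-value would describe something smaller than the week-8 effect. If the effect faded, they would describe something larger. Section 2.9 says the trial is meant to inform the sample size of later definitive trials, so an averaged effect carried forward as the week-8 effect would mis-size them.

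**Working it through.** The plan gives no figure for the model's group effect, so there is nothing to reproduce first. The check is what the listed terms estimate.

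**Inputs from the protocol article**
- Target: SNOT-22 change from baseline to week 8 (section 2.6.1).
- Terms: participant random; group and visit fixed (section 2.12).
- Visits: baseline and weeks 1, 2, 4 and 8 (abstract).
- Allocation 1:1 (section 2.5).

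**Assumptions**
- SNOT-22 is recorded at all of these visits.
- Data are complete.
- The effect follows one of several onset shapes, scaled so that the week-8 effect is 1.00.

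**Formula.** Let δ_t be the true group difference at visit t, T the number of modelled visits and V the within-participant covariance. In a main-effects model with balanced arms the expected group coefficient is Σ w_t δ_t, with w = V⁻¹1 / (1′V⁻¹1). A random participant effect alone implies equal variances and equal correlations, so every w_t is 1/T and the coefficient is the plain average of the δ_t. Computed with correlations of 0.3, 0.5 and 0.7, the result was the same each time.

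**Numbers, change scores at weeks 1, 2, 4 and 8 (T = 4)**
- Linear onset, δ_t = t/8: (0.125 + 0.25 + 0.5 + 1)/4 = 1.875/4 = 0.469.
- Equal steps per visit: (0.25 + 0.5 + 0.75 + 1)/4 = 0.625.
- Exponential onset, δ_t = (1 − e^(−t/τ))/(1 − e^(−8/τ)):
  - τ = 1 week: (0.632 + 0.865 + 0.982 + 1)/4 = 0.870.
  - τ = 2 weeks: (0.401 + 0.644 + 0.881 + 1)/4 = 0.731.
  - τ = 4 weeks: (0.256 + 0.455 + 0.731 + 1)/4 = 0.610.
- Constant from week 1: 4/4 = 1.00.

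**Raw scores with baseline as a fifth visit.** Randomisation makes the expected baseline difference zero, so each sum is divided by 5 instead of 4.

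| Onset | Change scores, 4 visits | Raw scores with baseline, 5 visits |
|---|---|---|
| Linear in time | 0.469 | 0.375 |
| Equal steps | 0.625 | 0.50 |
| Exponential, τ = 4 | 0.610 | 0.488 |
| Exponential, τ = 2 | 0.731 | 0.585 |
| Exponential, τ = 1 | 0.870 | 0.696 |
| Constant from week 1 | 1.00 | 0.80 |

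Two limiting cases: raw scores at baseline and week 8 only give (0 + 1)/2 = 0.50. Week-8 change as the only response gives 1.00, but then a visit factor has no purpose.

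**Simulation check.** The settings were 23 per arm, correlation 0.5, linear onset, a true week-8 effect of 1.00 and 150 runs. The group-plus-visit model gave a mean group coefficient of 0.45 (expected 0.469). With the interaction added, the week-8 contrast averaged 0.98.

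**The case against.** The strongest reply is that section 2.12 lists factors and does not say the list of model terms is complete. The article condenses a fuller protocol (version 1.1, section 2.2), and interactions, contrasts and covariance structure are often left to that document or to an analysis plan. This stands in part: a reader might infer that the plan rules out an interaction, and the text does not say so. But the article chose to state the terms, and those terms do not target its own primary outcome.

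Second, the repeated measures ANOVA promises a comparison at each visit, which would include week 8. This shows interest in visit-specific differences. It does not settle which result is primary, because the mixed model is the method named for the primary outcome.

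Third, the averaging does no harm for change scores if the effect is constant from week 1. That is correct, but the protocol neither states nor justifies such constancy.

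Two stronger readings are tempting and are not supported:
- *Inflated type I error.* A random participant effect imposes equal correlation on unequally spaced visits, so one might infer that the planned test rejects too often. For the listed terms with complete balanced data, the group test reduces to a t test on participant means, which is valid whatever the within-participant correlation. Checked under decaying correlations with 23 or 29 per arm, that test rejected in 4.8% to 5.4% of 20,000 runs per setting. Too small a week-8 standard error becomes a risk only if an interaction is added and the random-intercept covariance is kept.
- *A quantified loss of power.* This would need a week-8 effect and a covariance that the documents do not give. Section 2.9 states that "A formal power calculation has not been performed" and that "a minimal effect size of 0.25 and dropout rate of 20% have been assumed for this trial". At 0.25 SD, a simple two-group comparison at week 8 has only about 13% to 16% power with 23 to 29 per arm, so a power contrast built on a large effect would not describe this trial.

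**Conclusion.** The mismatch is real. As listed, the terms give one visit-averaged difference, while the primary outcome is the week-8 change. For change scores the two agree if the effect is constant over the modelled post-baseline visits or if week-8 change is the only response. Otherwise they agree only by chance cancellation.

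Under the increasing onset shapes examined, the group term recovers 47% to 87% of the week-8 effect for change scores and 38% to 70% if baseline is a modelled visit. These ranges rest on assumed onset shapes, on SNOT-22 being recorded at weeks 1, 2, 4 and 8, and on complete data. They illustrate the size of the problem and do not predict this trial's result.

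This should be fixed. It is not a fatal flaw: the trial is presented as exploratory groundwork for larger studies, the list of terms is not declared exhaustive, and a fuller document may already contain the interaction.

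**What to change.** Amend section 2.12 to state that:
- the mixed model is fitted to change from baseline in SNOT-22, with group, visit and group-by-visit as fixed effects;
- the primary analysis is the between-group difference at week 8, with its 95% confidence interval and p-value;
- differences at other visits, and the repeated measures ANOVA if it is kept, are secondary.

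Once the interaction is in, replace the random-intercept covariance with one that does not force equal correlation across unequally spaced visits, for example an unstructured matrix. With four visits that means 4 × 5/2 = 10 covariance parameters instead of 2, a small cost for 58 participants.

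The change takes about two sentences of text and minor edits to the model code. It needs no extra data or visits. If the full protocol or analysis plan already specifies this model, cite it in section 2.12 and make the wording agree.

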#### Inclusion criteria

2.4.1

Participants will be considered eligible for inclusion if they meet the following criteria:

(1)Men or women aged 19 to 60 years at the screening visit;(2)A diagnosis of CRS based on the presence of rhinosinusitis symptoms for more than 12 weeks.A.Presence of more than 2 major symptoms or 1 major symptom with 2 minor symptoms:i.Major symptoms: facial pain/pressure, nasal obstruction/blockage, nasal discharge/purulence/discolored postnasal drainage, hyposmia/anosmia, purulence observed in the nasal cavity on examinationii.Minor symptoms: headache, fever, halitosis, fatigue, dental pain, cough, ear pain/pressure/fullnessB.A diagnosis of rhinosinusitis based on paranasal sinus computed tomography (CT) findings.(3)A Sino-Nasal Outcome Test-22 (SNOT-22) score of ≥ 20 at the screening visit(4)Ability to comprehend the purpose and process of the study as well as the properties of the investigational drug and voluntary provision of written informed consent

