### Randomization and allocation concealment

2.7

A statistician will generate random allocation numbers using a computer program [Strategic Applications Software (SAS), version 9.4; SAS Institute Inc., Cary, NC]. The generated numbers will be sealed in opaque envelopes and stored in double-locked cabinets. Participants who fulfil all inclusion criteria will be assigned to 1 of the 2 groups via blocked randomization.

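### The primary model omits baseline SNOT-22, which is already collected: the comparison stays valid, but it loses some precision and shifts with any chance baseline imbalance

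*Protocol article*

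**What the plan says.** All references are to the protocol article.

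- **Outcome** (section 2.6.1): "The primary outcome will be the mean change in the SNOT-22 score from baseline to 8 weeks".
- **Measurements** (abstract, methods): "Data will be collected from the participants at baseline and at 1, 2, 4, and 8 weeks after random allocation".
- **Model** (section 2.12): an MMRM that "sets participants as a random factor and the group and visit as fixed factors". It "will be performed to analyze between-group differences in the primary and secondary outcome measures".
- **Baseline** (section 2.12): "Baseline differences between groups will be assessed using an independent 2-sample *t* test or the Wilcoxon rank-sum test for continuous variables". No adjustment for baseline is described. Symptom severity enters only as a subgroup factor.
- **Allocation** (section 2.7): participants are "assigned to 1 of the 2 groups via blocked randomization". The text names no stratification by baseline score.
- **Size** (section 2.9): 58 participants, 29 per arm, with an assumed effect size of 0.25 and 20% dropout.

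**The concern.** The section names the terms of the model, and baseline SNOT-22 is not one of them. Comparing changes from baseline without a baseline covariate fixes the slope of the week-8 score on the baseline score at 1. If the true slope is lower, two things follow. Part of the baseline variation stays in the error, so the confidence interval is wider than it need be. And the arm that happens to start worse will tend to show the larger improvement, whatever the treatment does.

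In a trial of this size, a chance imbalance that matters relative to an effect of 0.25 SD is quite possible. Significance tests of baseline differences do not alter the estimate. The variable that would correct for imbalance is already in the data.

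**Working it through.** **Inputs.** From the documents: 29 per arm; effect size 0.25; 20% dropout, which leaves about 29 × 0.8 = 23 per arm. Assumed, because the documents give no value: the baseline to week-8 correlation rho (0.3, 0.5, 0.7) and the ratio s of the week-8 SD to the baseline SD (1 and 1.25). The protocol gives no precision figure to reproduce. Baseline SD is set to 1 throughout.

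**1. Size of a chance imbalance.** The SE of the baseline difference is √(2/29) = 0.263 SD, so its 95% range is about ±0.51 SD. With 23 per arm the SE is √(2/23) = 0.295 SD.

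**2. Effect of an imbalance on the estimate.** Let D0 be the baseline difference and β the slope, β = rho × s. Given D0, the expected week-8 difference is (effect + β·D0). The expected difference in changes is therefore effect - (1 - β)·D0. At β = 0.5, a one-SE imbalance shifts the estimate by 0.5 × 0.263 = 0.13 SD. That is 0.13/0.25, about half the assumed effect size. At β = 0.3 the shift is 0.7 × 0.263 = 0.18 SD; at β = 0.7 it is 0.3 × 0.263 = 0.08 SD.

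The protocol does not say which SD the 0.25 refers to. At rho = 0.5 with equal SDs the SD of the change is √(2 × 0.5) = 1, the same as the SD of the score, so the comparison holds on either reading.

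**3. Precision, simple week-8 contrast.**

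- Change score: variance per participant 1 + s² - 2·rho·s.
- Baseline-adjusted: s²(1 - rho²).
- Difference between the two: (1 - β)², which is never negative.

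| s | rho | Change | Adjusted | Ratio | SE reduction |
|---|---|---|---|---|---|
| 1 | 0.3 | 1.400 | 0.910 | 0.650 | 19% |
| 1 | 0.5 | 1.000 | 0.750 | 0.750 | 13% |
| 1 | 0.7 | 0.600 | 0.510 | 0.850 | 8% |
| 1.25 | 0.3 | 1.813 | 1.422 | 0.784 | 11% |
| 1.25 | 0.5 | 1.313 | 1.172 | 0.893 | 5.5% |
| 1.25 | 0.7 | 0.813 | 0.797 | 0.981 | 1% |

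**4. Cost of estimating the slope.** The adjusted variance is multiplied by about 1 + 1/(58 - 4) = 1.019. In the worst case, a slope of exactly 1, the SE would be √1.019, or about 0.9%, larger. In the last row of the table the gain is all but cancelled (0.981 × 1.019 ≈ 1.00).

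**5. Check by simulation** (20,000 trials, 29 per arm, equal SDs). SEs for change versus adjusted were 0.308 v 0.251, 0.260 v 0.228 and 0.203 v 0.189 at rho 0.3, 0.5 and 0.7. The change estimate correlated with the baseline imbalance at -0.59, -0.50 and -0.39. After adjustment the correlation was about 0.

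**The case against.** **The article is silent, not wrong.** The clause speaks of factors, a continuous covariate is not a factor, and the SAP may add one. It is true that the text excludes nothing. But it does name the model's terms, and a better model than the one named is available from data already in hand. That is a reason to amend the sentence, not to call the analysis faulty.

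**The response variable is not stated.** Section 2.12 does not say whether the model takes the change or the raw score with baseline as one of the visits. On the second reading, with unconstrained group-by-visit means and complete data, the week-8 contrast is still the difference in changes. Constraining the arms to a common baseline mean would recover the gain, but the article does not say this. It stands that the formulas above describe a single week-8 contrast and not the full repeated-measures model.

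**The size is uncertain.** This stands. Neither rho nor any SD is given, and the equal-SD figures are the favorable half of the table. A reader might convert them into participants: at rho = 0.5, 58/0.75 = 77. With s = 1.25 the same sum gives 58/0.893 = 65, so no single equivalent is supported.

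**The entry criterion.** A reader might infer that requiring "A Sino-Nasal Outcome Test-22 (SNOT-22) score of ≥ 20 at the screening visit" makes a slope of 1 an especially poor choice. It does not. If the screening score serves as baseline and the relation is linear, truncation lowers the correlation but leaves the slope unchanged, and it shrinks the baseline variance. The saving, (1 - β)² times that variance, therefore gets smaller. With an untruncated correlation of 0.5 and an assumed 31% cut, rho falls to about 0.37, the slope stays at 0.50, and the SE reduction is about 7%. The equal-SD formula at that rho would give 17%.

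**It is a feasibility-type trial.** Section 2.9 disclaims a formal power calculation and looks ahead to sizing a later trial. This limits the harm, but section 2.12 still plans a between-group comparison at two-sided 0.05.

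**Conclusion.** The point holds as a recommended improvement in efficiency. The named model leaves out a prognostic variable that is measured on everyone. The resulting loss of precision ranges from material (SE about 19% lower with adjustment at rho 0.3 and equal SDs) to negligible (about 1% at rho 0.7 and s = 1.25), depending on quantities the documents do not give. Conditional on an imbalance, the shift is about 0.13 SD per one-SE imbalance at an assumed slope of 0.5.

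A reader might go further and infer that the planned analysis is biased or its test invalid. The documents do not support that. Over repeated randomization the comparison of changes is unbiased and the type I error is intact; the shift exists only given the imbalance that happens to occur. Nor do the planned baseline significance tests damage anything: they are presented as a description of the groups and do not enter the estimate.

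**What to change.** In section 2.12, add baseline SNOT-22 as a fixed covariate, preferably with a baseline-by-visit term, to the primary MMRM, and state that the model is fitted to the post-baseline visits (weeks 1, 2, 4 and 8). Treat each secondary outcome in the same way with its own baseline value. The response can remain the change: once baseline is a covariate, the group contrast is the same for the change and for the raw score.

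The cost is one phrase, no new data, and one degree of freedom for the main effect, or four with baseline-by-visit over four visits (1 + 3). Replacing the baseline significance tests with a purely descriptive table is optional and does not affect the result.

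### The repeated measures ANOVA for differences at each visit overlaps the MMRM at week 8 and does not by itself give per-visit differences; per-visit contrasts should come from one MMRM with a group-by-visit term

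*Protocol article*

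**What the plan says.** All of the following is in the protocol article.

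- **Statistical analysis, analysis set.** The measured variables, primary and secondary outcomes included, "will be assessed using the full analysis set based on intention-to-treat principles". The per-protocol set is the only analysis called a sensitivity analysis.
- **Statistical analysis, first between-group method.** An MMRM "which sets participants as a random factor and the group and visit as fixed factors". Its stated role is to compare the groups on every primary and secondary outcome. No group-by-visit term is named.
- **Statistical analysis, second between-group method.** After the within-group before/after tests, in the same sentence, "repeated measures analysis of variance will be used to assess differences between groups at each visit".
- **Statistical analysis, significance level.** One two-sided 0.05 level covers everything.
- **Primary outcome.** "The primary outcome will be the mean change in the SNOT-22 score from baseline to 8 weeks".
- **Abstract, Methods and analysis.** "Data will be collected from the participants at baseline and at 1, 2, 4, and 8 weeks after random allocation". Week 8 is therefore one of the visits.
- **Sample size.** There is no formal power calculation. A minimal effect size of 0.25 and a "dropout rate of 20% have been assumed for this trial", giving 58 participants, 29 per group.

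**The concern.** Three things do not fit together.

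First, the ANOVA does not match the purpose given for it. Its usual F tests address an overall group effect, a visit effect and their interaction. A group difference at a given visit needs extra contrasts or separate tests, and the text names neither.

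Second, the MMRM as worded does not match the primary outcome. With group and visit as the only fixed factors, the group coefficient is one difference assumed constant over visits, while the primary outcome is the change at week 8. The only analysis described as visit-specific is then the ANOVA, so the week-8 comparison could fall to it by default.

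Third, both methods can produce a week-8 group comparison, and the ANOVA is not marked as supportive. If they disagree, the text leaves room to argue over which week-8 figure to report. One likely source of disagreement is missing data, because the classical ANOVA uses only participants with every visit and the MMRM uses all observed visits. The trial is meant to inform later definitive trials, so an ambiguous week-8 estimate would be carried forward.

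**Working it through.** **The plan's own figure.** The plan gives no number for this analysis. Its total of 58 is context only: 23 per group before dropout would give 23 / 0.8 = 28.75, rounded up to 29 per group, or 58. The pre-dropout number and the power are not stated, so 58 cannot be fully reproduced.

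**Step 1: what each model estimates.** Take assumed true group differences of 0.1, 0.2, 0.35 and 0.5 SD at weeks 1, 2, 4 and 8 (my values, for illustration). The simple average over visits is (0.1 + 0.2 + 0.35 + 0.5) / 4 = 0.2875 SD, against 0.50 SD at week 8. A main-effects model targets something like the former, and the primary outcome is the latter. The same gap separates the ANOVA's overall group test from a week-8 difference.

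**Step 2: the two readings of the ANOVA clause.**
- *Classical complete-case form.* Anyone missing a visit is excluded. At the stated 20% dropout, 58 × 0.8 = 46.4, so about 46 are analysed and about 12 are lost.
- *Likelihood fit of a repeated measures model.* Nobody with some data is lost, but the analysis is then the MMRM under another name.

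The plan does not say which form is meant.

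**Step 3: loss of precision in the complete-case form.** The right comparator is a likelihood model on the same data, which also lacks week-8 values for dropouts. Assume all dropouts are seen up to week 4, and let r be the week-4 to week-8 correlation. Then

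SE(completers) / SE(likelihood) ≈ 1 / √(1 − r² × 12/58).

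- r = 0.4: 1 / √(1 − 0.0331) = 1.017
- r = 0.6: 1 / √(1 − 0.0745) = 1.039
- r = 0.7: 1 / √(1 − 0.1014) = 1.055

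The standard error is about 4% wider at r = 0.6, and about 2% to 5% wider over the range.

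**Step 4: possible bias in the complete-case form.** This is a simulation in which every parameter is assumed: 29 per arm, baseline plus four visits, correlation 0.6 between any two visits, and the true differences of Step 1. Dropout is more likely after a bad last score and more likely on placebo, tuned to leave about 46 completers. The likelihood model has separate group-by-visit means and a known covariance.

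| Analysis | Mean week-8 difference |
|---|---|
| Truth | 0.50 SD |
| Completers only | about 0.37 SD |
| Likelihood model | about 0.50 SD |

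In this scenario the completers understate the difference by about 0.13 SD. The size comes entirely from the assumed dropout rule.

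**The case against.** The strongest reply is that the clause is condensed wording for a secondary description. The MMRM is expressly assigned to between-group differences in the primary and secondary outcomes, and the ANOVA comes later, alongside the within-group tests. The Primary outcome section already fixes week 8. Simple-effect contrasts after a repeated measures ANOVA are routine, and missing-data handling is commonly left to the full protocol or SAP. Much of this stands, and it rules out several stronger readings that a reader might infer.

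- *The ANOVA contradicts the intention-to-treat set.* Not established. The full analysis set is stated for all measured variables and nothing exempts the ANOVA. Deletion of incomplete participants belongs to one unstated procedure.
- *Nothing says which method counts.* Too strong, given the MMRM's assignment. What remains is that the ANOVA overlaps it at week 8 without a supportive label, and that the MMRM as worded is not specific to week 8.
- *Sphericity fails across unequally spaced visits.* Not to the point. That assumption concerns the visit and group-by-visit tests, not a group contrast at a single visit.
- *The standard error is 12% wider.* √(58/46) = 1.123 compares completers with a trial that has no missing data. Against a likelihood model it is about 4%.
- *The bias takes up 84% of the assumed effect.* If placebo dropouts were exactly the worst fifth at week 4, the completers' placebo mean would shift by 0.350 × 0.6 = 0.21 SD. That is a one-arm shift; a similar mechanism in the other arm would largely cancel it. The ratio 0.21 / 0.25 = 84% also presumes that 0.25 is a standardised mean difference, and the Sample size section gives no metric. If it is Cohen's f for two equal groups (d = 0.5), the share is 42%.
- *Four visits inflate the error rate to 18.5%.* 1 − 0.95⁴ = 0.185 needs independent visits. At a correlation of 0.6 it is about 14%, and with a single primary time point the plan makes no four-visit claim.

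The reply does not remove the core. On its face, the only analysis described as visit-specific is one whose standard tests are not visit-specific.

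**Conclusion.** The point holds on the text alone in this form: two between-group analyses overlap at the primary time point; the MMRM as written gives a visit-averaged difference; and the ANOVA needs unstated contrasts to do what is asked of it. On either reading the clause adds nothing useful. Fitted by likelihood it duplicates the MMRM, and in its classical form it would exclude about 12 of 58 at the assumed dropout, which sits badly with the stated analysis set.

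The consequences are conditional. Bias at week 8 requires the classical form together with dropout that depends on symptoms and differs between arms. The illustrated 0.37 against 0.50 SD shows that it can matter, not how large it would be here. The precision loss is small, about 2% to 5% for correlations of 0.4 to 0.7.

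Severity is low to moderate, because the trial is described as a feasibility study without a formal power calculation.

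**What to change.** Make two linked edits in the Statistical analysis section.

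1. Add a group-by-visit term to the MMRM and state that its week-8 contrast for SNOT-22 is the primary analysis.
2. Replace the repeated measures ANOVA clause with group differences at weeks 1, 2, 4 and 8, each with a 95% confidence interval, taken from that same model for outcomes recorded at those visits. Label weeks 1, 2 and 4 as supportive.

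Both edits are needed. Deleting the ANOVA clause alone would remove the only stated per-visit comparison and leave a visit-averaged MMRM.

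The cost is a two-clause edit and a few extra parameters: with two groups and four post-baseline visits, (2 − 1) × (4 − 1) = 3 interaction terms. No new data are needed, and one analysis is removed.
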